### Statistical Analysis

IBM’s Statistical Package for the Social Sciences (SPSS) is utilized for the statistical analyses of the obtained data. Histograms (visual inspection) are used to ascertain whether variables are normally distributed. A significance level (alpha) of 0.05 is applied to all analyses unless stated otherwise. Differences in baseline characteristics of the study groups are tested using the independent *t*-test (for continuous, normally distributed data), the Mann–Whitney test (for non-normally distributed or ordinal data), or the chi-square test (for categorical data).

Assumptions for linear regression will be checked for all outcomes, including normality of residuals and homogeneity of variances. Where necessary, transformations (e.g., log transformation) were applied to meet model assumptions.

Difference between groups in %TWL, %EWL, and GERD-HRQoL at 5 years postoperative will be assessed using the independent *t*-test or Mann–Whitney test (for normally or non-normally distributed data, respectively). Baseline characteristics related to both the type of surgery and outcome variables (with *p*-value < 0.15) will be considered confounders in the analyses. If one or more confounders are identified, linear regression models will be used to assess differences between groups in %TWL, %EWL, and GERD-HRQoL at 5 years postoperative, each adjusted for relevant confounders.

The difference between groups in the reduction of obesity complications at 5 years postoperative will be tested using chi-square tests for each comorbidity. Holm-Bonferroni correction will be used to correct for multiple testing.

Chi-square tests will be used for the difference between groups in change of scores of the questionnaires, early and late dumping, and reflux. Additionally, a linear mixed model analysis will test the difference in change in the subscales of the SF-36 and OBESI-Q over time between groups.

The difference in the total number of complications between groups will be tested with independent *t*-tests or Mann–Whitney tests (for normally or non-normally distributed data, respectively).

Missing data will be reported if known. A sensitivity analysis will be performed for the primary outcome: analysis of the data “as-is” (without imputation) will be compared with the results of the analysis where missing data is imputed.

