### Quality of Life

Participating patients are asked to complete three questionnaires pre- and postoperatively during the follow-up period, the SF-36, OBESI-Q, and GERD-HRQoL, to assess quality of life.

The SF-36 questionnaire includes 36 items and measures eight health concept scales: Physical Functioning, Role-Physical, Bodily Pain, General Health, Vitality, Social Functioning, Role-Emotional, and Mental Health. The raw scores of each subscale are transformed to a 0–100 scale, where higher scores indicate better functioning or well-being. A minimum of 50% of the items in each subscale must be answered to yield a viable result [17].

The OBESI-Q questionnaire includes a set of six selected subscales from the BODY-Q that have been individually validated for Dutch practice [18, 19]. The BODY-Q measures four overarching domains. Each domain includes four or more independently functioning scales. Scales chosen in OBESI-Q include eating behavior, social, psychological, physical function, body image, and sexual. Scores for each outcome are calculated by summing up the points for each subscale. To enhance the interpretability of the sum score, it is converted to a total score on a scale of 0 to 100, where higher scores indicate better functioning or well-being.

The GERD-HRQoL questionnaire includes 18 items to measure the impact of GERD on sleep, exercise, diet, need for medication, sex life, work, social activity, and psychological well-being [20]. The total score is calculated by summing up the individual item scores, with no transformation of the raw scores into a scaled score required. The optimal score is 0, which indicates that the individual is asymptomatic across all categories, while the lowest possible score is 50, indicating complete incapacitation in all categories.

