### Sample Size Calculation

In order to obtain mid-term results, a 5-year follow-up period has been selected, consistent with standard practices in Dutch metabolic bariatric surgery. A total of 63 patients per group is necessary to detect a 5% difference %TWL between groups 5 years post-surgery. This calculation is performed using PASS software, with parameters set at power = 80%, alpha = 0.05, standard deviation = 10%, and average %TWL of group 1 vs. group 2 being 32 vs. 27, assuming a two-sided independent *t*-test.

Jense et al. observed a loss-to-follow-up (LtfU) ranging from 21 to 58% three to five years postoperatively [21]. To have sufficient power for the 5-year analysis, this study takes into account a LtFU of 40%, assuming that actively contacting patients will reduce LtFU at 5 years postoperatively. Based on a required sample of 63 individuals per group and an expected LtFU of 40%, we aim to include 210 patients for this study, 105 per group.

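### The primary %TWL test is left to a look at histograms, so the 5-year mean difference that the trial is sized on may not be what is tested or reported

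*Protocol article*

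**What the plan says.** All places are in the protocol article.

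- **Sample Size Calculation** states the target as a difference in means: "A total of 63 patients per group is necessary to detect a 5% difference %TWL between groups 5 years post-surgery", with "average %TWL of group 1 vs. group 2 being 32 vs. 27", "parameters set at power = 80%, alpha = 0.05, standard deviation = 10" percent, and "assuming a two-sided independent *t*-test".
- **Statistical Analysis** does not carry that test forward. Normality is judged as follows: "Histograms (visual inspection) are used to ascertain whether variables are normally distributed". The 5-year comparison of %TWL, %EWL and GERD-HRQoL is then a t-test if the data are taken as normal and a Mann–Whitney test if not. If baseline variables pass a screen as confounders, linear regression is used instead.
- A separate paragraph of the same section deals with the assumptions of linear regression for all outcomes and adds: "Where necessary, transformations (e.g., log transformation) were applied to meet model assumptions". It gives no rule for zeros and none for returning to a difference in points.
- **Quality of Life** says of GERD-HRQoL: "The optimal score is 0, which indicates that the individual is asymptomatic across all categories".

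**The concern.** The trial is sized to answer one question: do mean 5-year %TWL values differ, and by how many points? A Mann–Whitney test answers another: does a randomly chosen patient in one arm tend to have a higher value than one in the other? The two agree when one distribution is a shifted copy of the other, and need not agree otherwise. Under the plan, which question becomes primary depends on how a histogram strikes the analyst at the end, with no threshold to hold the judgement to.

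At stake is first the estimand. If Mann–Whitney is chosen, its result comes with no estimate of the 5-point difference in means. The second matter is analyst freedom: two analysts could look at the same histogram and defend different primary tests. In a trial described as non-blinded, that choice is best closed in advance.

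A smaller point concerns GERD-HRQoL. The one transformation that the article names cannot be computed at that instrument's best score.

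**Working it through.** **1. Reproduce the plan's figure.** Inputs from Sample Size Calculation: difference 5, SD 10, two-sided alpha 0.05, power 80%.

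n per group = 2 × (1.960 + 0.842)² × 10² / 5² = 62.8, so 63. Allowing for 40% loss to follow-up: 63 / (1 − 0.40) = 105 per group, 210 in total. The stated figures reproduce. The exact t calculation gives 63.8 (64 per group), and 79.5% power at 63; the gap is immaterial here. The calculation is for a difference in means throughout.

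**2. Power if Mann–Whitney replaces the t-test on normal data.** Its asymptotic relative efficiency is 3/π = 0.955, and 63 × 0.955 = 60.2, so 63 per arm behave like about 60. Exact t-test power at a standardised difference of 5/10 = 0.5 is 79.5% with 63 per arm and 77.5% with 60: a loss of about 2 points.

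**3. Simulation of the selection rule.** There were 10,000 trials per scenario with 63 per arm. Because a visual rule cannot be simulated, a Shapiro–Wilk p-value below 0.05 in either arm stood in for it (an assumption). The Monte Carlo standard error near 5% is √(0.05 × 0.95 / 10,000), about 0.2 points.

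| Scenario | t-test | Mann–Whitney | Selected by rule | Smaller p-value |
|---|---|---|---|---|
| No difference, normal | 5.2% | 5.0% | 5.3% | 6.1% |
| No difference, gamma (shape 4) in both arms | 5.1% | 5.3% | 5.3% | 6.5% |
| 5-point difference, normal | 79.9% | 77.9% | 79.9% | 81.5% |
| 5-point difference, gamma (shape 4) in both arms | 79.9% | 85.5% | 85.4% | 86.7% |
| Equal means and SDs, gamma (shape 1.5) v normal | 5.0% | 10.3% | 10.3% | 11.9% |
| Equal means and SDs, opposite skew (gamma, shape 2) | 5.3% | 25.9% | 25.9% | 27.4% |

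Entries are the share of trials with p < 0.05. The t-test holds about 5% error in every row without a mean difference and about 80% power in both rows with one. That supports the statement that a comparison of means with 63 per arm does not need normal data. The last two rows show that Mann–Whitney can reject when the means are equal; their shapes are assumed for illustration.

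**4. Log transformation.** The logarithm of 0 does not exist, so a plain log cannot be taken of the asymptomatic GERD-HRQoL score. On %TWL, a log would turn a difference of 5 points into a ratio (32/27 = 1.185 on the planning means). It would also fail at values of 0 or below. With mean 27 and SD 10, and assuming normality, P(%TWL ≤ 0) = Φ(−2.7) = 0.35% per control patient: 63 × 0.0035 = 0.2 patients expected, and 1 − (1 − 0.0035)^63, about 20%, for at least one.

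**The case against.** The best defence is that little harm has been shown. The rule would normally select the t-test for near-normal data, which is exactly where Mann–Whitney loses its 2 points of power. When both arms have the same skewed shape, Mann–Whitney is the more powerful test (85.5% against 79.9%). Applied mechanically, the rule keeps type I error at about 5.3%. This stands, and it limits the size of the point. It does not supply a criterion for the histogram, and it does not turn a rank comparison into an estimate of the mean difference.

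A reader might also infer several stronger things that the article does not support:

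- *That the histogram decides on the log transformation too.* It decides only between the t-test and Mann–Whitney. Transformation belongs to the separate check of regression assumptions, and log is only an example there.
- *That the tests break down at a GERD-HRQoL score of 0.* Both are defined at 0; only a plain log is not.
- *That all asymptomatic patients would be dropped.* The article assigns log to no particular outcome and does not rule out an offset. Such a loss would follow from a later analytic choice, not from a stated plan.
- *That the histograms are inspected by arm with allocation known.* The trial is described as non-blinded, but the article does not say who inspects them or whether they are split by arm.
- *That type I error reaches 10% or 26%.* Those figures need equal means with different shapes in the two arms, which is an assumption. The 6.1% to 6.5% figures need the analyst to take the smaller p-value, which the plan does not provide for.

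**Conclusion.** The point holds in limited form. The sample size rests on a difference in mean 5-year %TWL tested with a t-test, while the analysis section lets a visual judgement without a criterion replace that test with one that has a different hypothesis and no estimate of the planned quantity. The defect is an effect measure left open until the data are seen.

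Its numerical size is modest: about 2 points of power under normality, and type I error of about 5.3% when the arms share a shape. Both rest on the plan's SD of 10 and 63 evaluable patients per arm; the second also on Shapiro–Wilk as a stand-in for the eye. Larger errors are possible if the arms differ in shape, but the article gives no basis for saying how likely that is.

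The GERD-HRQoL point is secondary: the named example transformation does not suit a scale whose best score is 0. For %TWL, the difficulty with non-positive values is rare on the planning figures; the better reason not to log it is that the result would no longer be in percentage points.

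**What to change.** - State that the primary analysis is the between-group difference in mean 5-year %TWL with its 95% confidence interval, whatever the histogram shows. Use either a Welch t-test or one linear model with robust standard errors and covariates named in advance. The article at present has no such model: regression enters only after a screen of baseline variables, so if the model is preferred its covariates must be listed now.
- Do not transform %TWL in the primary analysis.
- Keep Mann–Whitney as a named sensitivity analysis for %TWL.
- Analyse GERD-HRQoL on its untransformed scale, with a bootstrap confidence interval if it is skewed.

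The cost is wording only. The sample size stays at 63 evaluable and 105 randomised per group, 210 in total. The change should be dated before the 5-year outcomes are examined, because a test fixed afterwards is not pre-specified.

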### Secondary Outcomes

%EWL: defined as the percentage of excess weight lost relative to the excess weight at the time of informed consent [22]. In formula$${\%EWL}=\frac{\text{preoperative BMI}-\text{ current BMI}}{\text{preoperative BMI}-25}\text{x}\;100$$Reduction or remission of obesity complications: Obesity complications include type 2 diabetes mellitus, hypertension, joint complaints, dyslipidemia, OSAS, and GERD. (Inter)national guidelines are used as reference [23, 24]. Reduction is defined as a decrease in symptoms, medication use and/or dosage, and/or laboratory results. Remission is defined as the state in which a patient no longer reports symptoms, does not require any medication for their comorbidity, and/or has normalized laboratory results. In case of type 2 diabetes, remission is defined if glycosylated hemoglobin (HbA1c) is 43 mmol/mol without the use of pharmacotherapy as per local protocol [23] In case of OSAS, remission is considered when there is a discontinuation of CPAP treatment.Quality of life: assessed using the SF-36, OBESI-Q, and GERD-HQoL questionnaires at earlier mentioned follow-up intervals compared to pre-operative baseline measurements.Presence of early and late dumping: determined based on symptoms reported by patients and evaluated by expert physicians during the follow-up period.Complications: All complications during follow-up and until 5 years postoperative are included in the analysis, regardless of their potential relation to the ring. Complications are categorized as perioperative, early (< 30 days, with or without readmission), and late (> 30 days, with or without readmission). Possible complications include bleeding, wound infections, intra-abdominal abscesses, anastomotic leaks, deficiencies (especially in vitamin B12 and ferritin), conversions, migration, erosion, and slipping of the ring. Laboratory reference values are used for deficiencies.

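### The Holm correction, on its natural reading, stops at the six comorbidity tests, leaving 14 quality-of-life subscale tests each at 0.05 and reflux under two different error rules

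*Protocol article*

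**What the plan says.** All references are to the protocol article. Statistical Analysis fixes the error level for the whole plan: "A significance level (alpha) of 0.05 is applied to all analyses unless stated otherwise".

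The exception comes in the paragraph on obesity complications. The group difference at 5 years "will be tested using chi-square tests for each comorbidity", and the next sentence reads "Holm-Bonferroni correction will be used to correct for multiple testing". Secondary Outcomes lists the conditions: "Obesity complications include type 2 diabetes mellitus, hypertension, joint complaints, dyslipidemia, OSAS, and GERD". That makes six tests, one of them GERD.

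The following paragraph turns to the questionnaires and symptoms: "Chi-square tests will be used for the difference between groups in change of scores of the questionnaires, early and late dumping, and reflux". It adds that "a linear mixed model analysis will test the difference in change in the subscales of the SF-36 and OBESI-Q over time between groups". The Quality of Life section gives the number of subscales: the SF-36 "measures eight health concept scales", and the OBESI-Q is "a set of six selected subscales from the BODY-Q". An earlier paragraph of Statistical Analysis tests GERD-HRQoL at 5 years together with %TWL and %EWL. None of these paragraphs names a correction or says that the results are exploratory.

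**The concern.** The plan accepts that several tests of one kind need joint error control, and provides it for six comorbidities. The larger family of 14 subscale tests gets no such control. Quality of life is a named secondary endpoint with formal tests, so one subscale with p below 0.05 could be reported as a benefit or a harm of the ring when it is a chance finding.

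Reflux adds an inconsistency of its own. One reflux outcome must pass Holm, while two others in the same section fall under the uncorrected default. The plan does not say which of the three carries the claim about reflux, so that choice could be made after the results are known.

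**Working it through.** **Inputs.** Default level 0.05 per test and six Holm-corrected comorbidities (Statistical Analysis, Secondary Outcomes). Eight SF-36 and six OBESI-Q subscales (Quality of Life). 63 evaluable patients per group, SD 10, difference 5, two-sided 0.05, power 80% (Sample Size Calculation). Correlation between subscale test statistics: not given, so a range is shown.

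**The plan's own figure.** The article states no family-wise error rate. Its sample size is used below to price the fix, so it is checked first. With the normal approximation, n = 2(1.96 + 0.842)² × 10²/5² = 62.8, so 63 per group; 63/(1 − 0.40) = 105 per group, 210 in total. This agrees with the article.

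**Size of the family.** 8 + 6 = 14 mixed-model tests. This is a lower bound for quality of life, because chi-square tests on change in questionnaire scores come on top.

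**Family-wise error with all 14 null hypotheses true.**

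- Independent tests: 1 − 0.95^14 = 0.51.
- Correlated tests: simulation (at least 200,000 draws) with z_i = √ρ·s + √(1 − ρ)·e_i, where s and the e_i are independent standard normal, counting any |z_i| > 1.96.

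| Correlation ρ | Chance of at least one false positive |
|---|---|
| 0 | 0.51 |
| 0.3 | 0.44 |
| 0.5 | 0.35 |
| 0.7 | 0.25 |
| 0.8 | 0.20 |
| 0.9 | 0.14 |

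The rate runs from 0.14/0.05 = 2.8 times to 0.51/0.05 = about 10 times the nominal level. The expected number of false positives is 14 × 0.05 = 0.7 at any correlation.

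**Comparison with the family that is corrected.** Six independent tests without Holm would give 1 − 0.95^6 = 0.26. The 14 subscales still carry about that much error at a correlation of 0.7.

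**Reflux, set side by side.**

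| Outcome | Error rule as written |
|---|---|
| GERD, as one of six comorbidities | Holm; 0.05/6 = 0.0083 if it has the smallest p-value |
| Reflux, chi-square test | Default 0.05 |
| GERD-HRQoL at 5 years | Default 0.05 |

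**Cost of Holm over the 14 subscales.** The first step compares the smallest p-value with 0.05/14 = 0.0036, for which z = 2.914. Treating a subscale contrast as a two-group comparison with a 0.5 SD effect and 63 per group, the standardised effect is 0.5 × √(63/2) = 2.806. Power at 0.05 is Φ(2.806 − 1.960) = 0.80. At the first Holm step it is Φ(2.806 − 2.914) = 0.46.

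**The case against.** The strongest reply is that the trial has one primary endpoint and its stated aim concerns %TWL alone. Secondary endpoints often go uncorrected in single-centre academic trials, and the finer rules may sit in an analysis plan that is not shown. It stands that the primary conclusion is safe. The rest does not dispose of the point, because the article is not silent: it sets the 0.05 default itself and corrects one secondary family but not the others.

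It also stands that the Holm sentence states no scope. Restriction to comorbidities is inferred from its position. If a wider family was meant, the text still needs to say so.

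Three stronger readings are tempting and are not supported.

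- **A false secondary claim is likely.** For the 14 subscales the chance exceeds one half only near independence. It is 0.35 at correlation 0.5, and it assumes that every null is true. Subscales of one questionnaire are likely to be correlated.
- **The error family is all 20 tests outside Holm.** Adding %EWL, GERD-HRQoL, early dumping, late dumping, reflux and total complications to the 14 gives 20, with a rate of 0.64 if independent and 0.42 at correlation 0.5. But by the article's formulas %EWL equals %TWL × BMI/(BMI − 25), with BMI the preoperative value, so its null cannot sensibly be true if the planned 32 versus 27 difference exists. Dumping and complications are safety outcomes, for which correction could hide harm.
- **A reflux result can bypass Holm, failing as GERD and then passing as reflux on the same question.** The comorbidity test concerns reduction of an existing condition, the separate reflux outcome is not defined, and GERD-HRQoL is a patient-reported score. They may ask different questions. What the text shows is unequal treatment of related outcomes.

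**Conclusion.** The point holds for the 14 quality-of-life subscales and for the inconsistent handling of reflux. On the natural reading of the Holm sentence, the family-wise false-positive rate for the subscales lies between 0.14 (correlation 0.9) and 0.51 (independence), against a nominal 0.05. These figures rest on a global null, equal correlations and normal test statistics. The direction does not depend on the exact correlation: the rate is well above 5% at every value tried. The reflux point needs no such assumption, since it follows from the text.

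The consequence is limited to what may be claimed about quality of life and reflux. The 5-year %TWL test and its sample size are unaffected. The change should be made before the 5-year analysis, but the trial's main conclusion does not depend on it.

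**What to change.** In Statistical Analysis:

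1. State which tests form the Holm family.
2. For the 14 SF-36 and OBESI-Q subscales, choose one of two rules. Either apply Holm within the 14, starting at 0.05/14 = 0.0036, or label them exploratory and report estimates with 95% confidence intervals and no claim of significance.
3. Name one reflux measure as the efficacy test of reflux, and report the others as estimates with confidence intervals.
4. Report %EWL as supportive of the primary outcome.
5. Report dumping, complications and new reflux as safety estimates with confidence intervals, without correction, so that signs of harm are not suppressed.

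This takes a few sentences and needs no new data or patients. If Holm is chosen, power at the first step for a single subscale falls from about 80% to about 46% under the assumptions above. The exploratory label avoids that loss, at the price of making no significance claim for quality of life.

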### Surgical Techniques

Standard surgical techniques are used in all study patients. A long and narrow pouch is formed from the angle of the lesser curvature to the angle of His. Calibration of pouch diameter is done loosely around a 34 fr nasogastric tube. A standard-length biliary limb of 150 cm for patients with BMI up to 50 kg/m^2^ or 180 cm for patients with BMI above 50 kg/m^2^ is drawn cranially in an antecolic antegastric position. A 30/40-mm stapled side-to-side gastro-jejunostomy is created with a linear endostapler. The remaining defect is closed with a 23-cm 3–0 absorbable V-loc running suture, starting the suture more proximally on the biliary limb and aligning this along the longitudinal stapling line of the pouch. In the intervention group, a silicone ring is placed 2 to 4 cm caudal to the gastro-esophageal junction. The chosen circumference of the silicone ring is 7.5 cm (approximately 24 mm internal diameter). The silicone ring is secured to the longitudinal staple line with a non-absorbable suture. Control of the integrity of the anastomosis and staple line is performed in both groups by air leak testing after the introduction of a gastric tube by the anesthesiologist. Additional sutures are placed in case of leakage.

The silicone ring is a CE-marked medical device by Bariatric Solutions, which consists of a silicone-coated blunt tip and a ring body with four locking positions. Once the ring is secured, the blunt tip will be cut off and removed.

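### Covariates for the primary 5-year %TWL comparison are picked by a p < 0.15 screen on the trial's own data; one prespecified adjusted model should replace the screen

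*Protocol article*

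**What the plan says.** All references are to the protocol article. The Statistical Analysis section plans an independent t-test, or a Mann–Whitney test if the data are not normal, for %TWL, %EWL and GERD-HRQoL at 5 years. It then defines confounders as "Baseline characteristics related to both the type of surgery and outcome variables", with a p-value threshold of 0.15, and continues: "If one or more confounders are identified, linear regression models will be used to assess differences between groups". No covariate and no candidate list is named. The same section states that "Differences in baseline characteristics of the study groups are tested", using t-tests, Mann–Whitney tests or chi-square tests.

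Study Design and Patient Selection says that allocation follows a computer-generated random sequence and that the trial is not blinded. The Sample Size Calculation rests on an unadjusted comparison ("assuming a two-sided independent" t-test) with "power = 80%, alpha = 0.05, standard deviation = 10" percent and "average %TWL of group 1 vs. group 2 being 32 vs. 27". In Surgical Techniques, baseline BMI determines part of the operation: "A standard-length biliary limb of 150 cm for patients with BMI up to 50", with a longer limb above that value.

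**The concern.** Among all randomised patients, an association between a baseline variable and arm is a chance event. Its p-value therefore says nothing about whether adjustment is useful. What makes a covariate worth including is that it predicts the outcome, and the precision gain comes whether or not it is balanced. The rule admits a predictor only when it happens to be imbalanced, so most strong predictors stay out of the model in most trials.

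Two things are at stake.

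- **Prespecification.** One half of the screen uses the 5-year outcome. The primary result could be a t-test, a rank test or a regression on an unknown covariate set, and nobody can say which until the outcomes have been seen. In an unblinded trial with no candidate list, that leaves room for discretion.
- **Efficiency.** When the arms are balanced on a predictor and it is left out, the unadjusted standard error is too large for the data at hand. The test then rejects less often than its nominal level and gives away power.

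**Working it through.** **Inputs from the Sample Size Calculation.** Two-sided alpha 0.05, power 80%, SD 10, difference 32 − 27 = 5, 63 evaluable per group, 40% loss to follow-up.

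**Assumed, because the article does not give them.** The share of %TWL variance explained by baseline variables (R²), the number of candidates screened, and how many of them are prognostic. The 0.15 threshold is read as applying to both associations.

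**Step 1: the plan's own figure.** n = 2(1.96 + 0.8416)² × 10² / 5² = 62.8, so 63 per group; 63 / 0.6 = 105 per group, 210 in total. This reproduces. The t-distribution version gives 63.8, so 64; t-test power at 63 per group is 79.5%.

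**Step 2: how often the rule adjusts.** A covariate unrelated to arm passes the arm screen with probability 0.15. A strong predictor nearly always passes the outcome screen, so it enters in about 15% of trials. A non-prognostic variable enters with probability 0.15 × 0.15 = 0.0225. With 10 candidates, 3 of them strong predictors, the chance that at least one enters is 1 − 0.85³ × 0.9775⁷ = 1 − 0.614 × 0.853 = 0.48. The simulations below give 40% to 47% for R² from 0.1 to 0.3.

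**Step 3: power available from a fixed ANCOVA.** The residual SD is 10√(1 − R²), so the standardised effect is 5 / [10√(1 − R²) × √(2/63)] = 2.806 / √(1 − R²). For R² = 0.1, 0.2 and 0.3 this is 2.96, 3.14 and 3.35. The normal approximation Φ(effect − 1.96) gives 84%, 88% and 92%. Simulation with one covariate gives 83.0%, 87.1% and 91.1%, slightly lower as expected with t quantiles.

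**Step 4: the rule itself, by simulation.** 63 per arm, SD 10, normal data, 10 candidates with 3 prognostic, 20,000 null trials and 10,000 with a 5-point difference. The ANCOVA uses exactly the three true predictors.

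| R² (assumed) | Size of rule | Power of t-test | Power of rule | Power of ANCOVA | Loss of rule against ANCOVA |
|---|---|---|---|---|---|
| 0 | 5.0% | 79.7% | 78.2% | 78.4% | 0.2 |
| 0.1 | 4.6% | 79.6% | 78.2% | 82.7% | 4.5 |
| 0.2 | 4.2% | 79.4% | 79.5% | 86.6% | 7.1 |
| 0.3 | 3.7% | 79.4% | 81.0% | 90.9% | 9.9 |

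Simulation error is about 0.15 points for size and at most about 0.4 points for power. The unadjusted t-test came out at 5.1% to 5.3% under the null in these runs, so the sizes shown lean slightly high. Smaller runs of the same setting (4,000 to 5,000 trials per cell) put the size at about 4.7%, 3.8% and 3.5% for R² = 0.1, 0.2 and 0.3, and the loss at about 4, 6 and 9 to 10 points. With a single candidate that is prognostic, the losses are about 3, 6 and 9 points.

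**Step 5: what if the named covariates are not the right ones?** In a run of 6,000 trials per cell at R² = 0.2, power was 80.5% for the rule and 87.4% for ANCOVA on the three true predictors. A fixed five-variable list containing only one of them gave 81.2%, and a list containing none gave 78.6%. At R² = 0.1 the rule and the one-predictor list both gave 78.2%, against 82.3% for the true predictors.

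The choice between t-test and Mann–Whitney by histogram was not modelled.

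**The case against.** The strongest reply is that nothing the plan promised is broken. It planned 80% power for an unadjusted t-test, and for R² up to 0.3 the rule delivers about 77% to 82% across the runs. The lost power is a gain forgone against an analysis the protocol never set out. The error is on the conservative side, and the comparator in the simulation knows the true predictors, as no real covariate list would. All of this stands, and it limits the severity.

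Three further points stand in part.

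- The 0.15 threshold may attach only to the outcome association, and the text does not say outright that regression replaces the unadjusted test rather than supplementing it. Either reading still leaves the covariates to be found in the data.
- If the 5-year comparison uses completers, with 40% loss assumed, imbalance there need not be pure chance. That is a reason to adjust for named predictors; it does not justify a significance screen, which can miss a relevant imbalance at about 63 per arm.
- Testing baseline differences is mainly a reporting preference once the tests no longer select covariates.

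A reader might also infer that BMI is an established predictor wrongly left out, because it sets limb length. The article does not show this: it says nothing on whether BMI or limb length predicts 5-year %TWL, and %TWL is already scaled to preoperative weight. BMI is a reasonable candidate, no more.

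The gap cannot be put down to a condensed article. The article states a working rule, and an analysis plan with fixed covariates would have to contradict it.

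**Conclusion.** The concern holds in a limited form. The primary model is chosen from the trial data, including the outcome, and this is so at any R². The numerical cost is conditional. If baseline variables explain 10%, 20% or 30% of the variance in %TWL, size falls to about 4.7%, 3.8% or 3.5%, and power is about 4, 6 or 9 points below an ANCOVA on the true predictors. If they explain nothing, size is nominal and the loss is about 1 point or less. These figures rest on assumed values of R² and of the number of candidates, and on reading the threshold as applying to both associations.

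Two stronger conclusions are tempting and not supported. The rule as modelled does not inflate type I error. Nor does it invalidate the sample size, which reproduces and whose power target is roughly kept. It is also not the case that any fixed list recovers the full gain: that depends on naming covariates that do predict outcome. This should be fixed, but it is not a fatal flaw.

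**What to change.** Delete the p < 0.15 screen. Before any 5-year data are examined, prespecify one primary linear model of 5-year %TWL on arm plus a short named list of baseline variables that are collected anyway and chosen on prior prognostic grounds, for example baseline BMI, age, sex and type 2 diabetes. Fit it whatever the observed balance, and report the unadjusted difference as supportive. Keep the list short, since variables that do not predict outcome bring no gain. Take the same approach for %EWL, and for GERD-HRQoL also include its preoperative score, which the Quality of Life section already has patients provide. Once the screen is gone, the baseline significance tests serve no purpose in the analysis and can give way to a descriptive table.

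The cost is a change of wording in the protocol or analysis plan, with no new data and no change to the sample size. The timing matters: a covariate list chosen after the outcomes are known cannot be shown to be independent of them.
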